#### Placebo

Placebo serves to minimize bias as to act as a control condition.

Given the three drugs and their side effects, the following harms during a single drug treatment are expected: temporary and reversible dizziness, tiredness, somnolence, euphoric mood, nausea, and headache.

### Rationale for the induction of hyperalgesia using high-frequency stimulation (HFS)

High-frequency electrical pulses delivered to the skin using a multipin electrode designed to preferentially activate cutaneous nociceptors is a validated and non-invasive procedure to induce a stable secondary hyperalgesia surrounding the location where HFS was applied due to central sensitization lasting at least 4 h [8, 9, 25]. We will assess the area of secondary hyperalgesia to pinprick and the intensity of pinprick hyperalgesia and dynamical mechanical allodynia. HFS induces a local skin flare response but does not cause long-lasting spontaneous pain.

### Intervention description {11a}

The IMPs will be (1) lacosamide (Vimpat®) film-coated tablets (composition: 2 × 100 mg lacosamide tablets); (2) pregabalin (Lyrica®) capsules (composition: 2 × 75 mg pregabalin capsules); (3) tapentadol (Palexia®) immediate release tablets (composition: 2 × 50 mg tapentadol immediate release tablet); and placebo capsules (composition: 2 × hard gelatine capsules filled with mannitol and colloidal silicon dioxide) (2).

Each IMP will be overencapsulated and administered as single oral dose (two capsules), in a double-blind, 4-period, crossover fashion where the study periods are separated by at least 1 week. All IMPs, except placebo, are registered medications in the countries that will participate in the trial. IMPs will be obtained from commercial stock [2].

As described for RCT3 [2], for the induction of hyperalgesia, HFS will be delivered to superficial nerve terminals using a multipin surface electrode similar to the electrode used in Klein et al. [8] and developed by MRC. The stimuli will be applied to the skin of the left volar forearm. The electrical pulses will be generated by a standard, CE-approved, constant-current electrical stimulator routinely used for clinical diagnostic purposes. The stimulation will consist in trains of 100-Hz pulses lasting 1 s and repeated five times, at an intensity sufficient to generate strong activity in small-diameter nociceptive afferents.

### Criteria for discontinuing or modifying allocated interventions {11b}

At the start of each of the four study periods, subjects will be excluded from the period if any of the criteria listed in Table 4 apply [2].

**Table 4 Tab4:** Exclusion criteria at study periods

	Exclusion criteria at study periods:	Justification / rationale
33	For female subjects of child bearing potential: positive or missing pregnancy test	To protect a fetus
34	Positive or missing urine test for drugs of abuse (opioids, amphetamines, benzodiazepines, cannabinoids).	Subject safety and to avoid interactions with, e.g., tapentadol (PD interactions, safety interactions)
35	Blood loss of 500 mL or more (e.g., owing to blood donation) since screening.	To ascertain the subject’s suitability for the study
36	Any other reason to exclude the subject according to judgment by the investigator	To avoid interference with the purpose of the study.
Temporary exclusion criteria at study periods. The subject is not excluded if some of these temporary exclusion criteria are met at screening of the study period. Instead, the study period may be postponed. If this is the case, all temporary exclusion criteria will be checked again.		
37	Alcohol consumption in the last 48 hours prior to the study period.	Subject safety and to avoid interactions with, e.g., tapentadol (PD interactions, safety interactions)
38	Intake of any drug including herbal medicines and other remedies except the following: contraceptives; oral paracetamol or ibuprofen up to the maximum recommended dose according SmPC, with last intake for both > 4 days prior to each study period for a self-resolving condition.	As described for screening visit
39	Changes in physical exercise activities, e.g., starting workout/training within 1 week prior to the study.	To avoid interference with the purpose of the study
40	Current pain within the last 4 days before the study period.	To avoid interference with the purpose of the study
41	Any transient, clinically relevant illness within 4 days before the period.	To ensure the subject’s good health
42	Incidentally not willing or able to comply with the requirements of the trial protocol or the instructions or to communicate meaningfully with the trial site staff.	To ascertain the subject’s suitability for the study
43	Incidentally unable to take oral medication.	Requirement for the study
44	Jet lag / irregular working hours / sleep restriction in the last 3 days before the period.	To avoid interference with the purpose of the study

Reproduced from [2]

### Strategies to improve adherence to interventions {11c}

At each study period, an oral dose of lacosamide, pregabalin, tapentadol, or placebo will be taken with 100 mL of plain water [2]. After intake of the study medication, the investigator will inspect the subject’s mouth to verify that the medication is swallowed.

### Relevant concomitant care permitted or prohibited during the trial {11d}

Prohibited drugs at screening and for each study period is described in Table 3 (Exclusion Criterion #28) and 3 (Exclusion Criterion #38), respectively.

### Provisions for post-trial care {30}

Suitable insurance for subjects will be in place at each site. A follow-up telephone call will be made between 7 and 14 days after the last study period to ensure the absence of adverse events. Otherwise, no post-trial care is foreseen as the study is conducted in healthy volunteers.

### Outcomes {12}

The objective of the study is to evaluate the effect of the study drugs on a set of biomarkers derived from peripheral nerve excitability.

### Rationale for the chosen biomarkers

Measurements of peripheral nerve excitability using threshold-tracking protocols are sensitive to membrane potential at the site of stimulation. Set of useful indices of axonal excitability collectively may provide insights into the mechanisms responsible for membrane polarization, ion channel function, and activity of ionic pumps during the process of impulse conduction [3, 4]. Standard NET assesses the function of large fibers. The nerve is stimulated directly, and the compound action potential is measured distally. Perception threshold tracking is a method where the membrane potential is assessed distally in the nerve fiber. With the use of small cathodes, the small fibers can be assessed. The subject will press a button when he/she feels a sensation, and the perception threshold is tracked.

### Primary and key secondary outcomes

The primary endpoints are the changes of the strength-duration time constant (SDTC) measured in large sensory fibers and in large motor fibers, both at the planned first PD time point post dosing relative to their pre-dose PD measurement (i.e., difference to period specific baseline). The SDTC is a measure for the dependency of the threshold current intensity related to the duration of a stimulus. These endpoints are determined four times per subject, once per period (i.e., once per different IMP administered). The primary analysis will concentrate on the comparison of the lacosamide vs. placebo effect, while the primary endpoints will also be tested in key secondary analyses. Lacosamide was chosen for primary outcome, as we expect this drug to act on the peripheral compartment that is the compartment assessed in RCT1.

The key secondary endpoint is the SDTC measured in small sensory fibers at the planned first PD time point post dosing relative to the pre-dose PD measurement (i.e., difference to period specific baseline).

### Definition of other prespecified analyses

Percentage change in motor and sensory threshold electrotonus (the amount of change in membrane excitability in response to long-lasting preceding de- or hyperpolarizing currents) (TEh (90–100 ms), TEh (peak, − 70%) and S2 accomodation) vs. baselineChange in refractoriness and relative refractory period in recovery cycle of nerve excitability (motor and sensory large fibers)*PK/PD analysis*. As both drug concentrations and biomarker responses are measured at several time points post drug administration, the relationship between drug levels and select biomarkers will be explored, and modeled

There are many other exploratory analyses and outcomes corresponding to the variety of drugs and time points when assessments are done, the collection of pain intensity and PROMs, etc. These are described in more detail in the statistical analysis plan.

### Participant timeline {13}

Figure 2 summarizes the participant timeline, which includes a screening visit, followed by four study periods and a follow-up telephone contact similar to RCT3 [2]. There will be an optional contact before the first study period. If screening of exclusion criteria for eligibility for period 1 shows that one or more temporary exclusion criteria are met, the start of period 1 can be postponed and re-scheduled [2]. Each subject is expected to be in the trial for approximately a minimum of 30 days and a maximum of 14 weeks.

**Fig. 2 Fig2:**
[figure not shown]
Timeline of the study which includes a screening visit, an optional contact, four study periods separated by at least 1 week, and a follow-up telephone contact. Reproduced from [2]

### Screening visit

As described previously for RCT3 [2], the following will be performed:
Explain the purpose of the research, the extent and burden of the procedures and assessments.Obtain informed consent.Assess subject handedness using the Edinburgh Handedness Inventory.Record demographic data.Record prior and concomitant medication.Record clinically relevant medical and surgical history.Assess inclusion criteria.Perform a focused neurological examination in the presence of any clinically evident sensory disorder and a physical examination if indicated from the medical history.Record a 12-lead electrocardiogram and verify absence of signs of second or third degree atrioventricular block.Perform urine pregnancy test.Collect a blood sample to verify normal renal and hepatic functions.Perform urine test for drug abuse (opioids, amphetamines, cannabinoids) and perform alcohol consumption check.Record psychosocial characteristics using patient-reported outcome measures and validated questionnaires.Instruct the subject on the study-specific procedures including how to use the rating scales.Demonstrate the test stimuli that will be used, induce sensitization at the left forearm using HFS and perform hyperalgesia testing 20 min after induction.Assess exclusion criteria specific for the screening visit.

### Optional contact before start of treatment period

The optional (telephone / email) contact will be after the screening visit and at the latest 48 h before the first study period with the purpose to arrange the time for the first study period and remind the subject of restrictions and ensure the subject had not taken prohibited drugs.

### Treatment periods: study periods 1, 2, 3, and 4

Each study period will be separated by at least 1 week. The subjects will have a light breakfast at home. The schedule of events is identical for all study periods and is provided in Table 5 and presented previously for RCT3 [2].

**Table 5 Tab5:** Detailed timetable of procedures and assessments in periods 1, 2, 3, and 4

Clock time	Time relative to dose (minutes)	Time relative to HFS (minutes)	Dose	HFS	PK	PD	Hyperalgesia testing**	PROMs	(D)rink (M)eal
08:00	− 150	− 60							
08:30	− 120	− 30						X	
09:00	− 90	0		X					
09:30	− 60	30				[1]			
10:00	− 30	60							
10:30	0	90	X						D
11:00	30	120							
11:15	45	135			[1]				
11:30	60	150				[2]			
12:00	90	180							
12:30	120	210					X		D
13:00	150	240			[2]				
13:30	180	270				[3]			
14:00	210	300							
14:30	240	330			[3]				M
15:00	270	360							
15:30	300	390						X	
16:00	330	420							
16:30	360	450				[4]			
17:00	390	480							
17:30	420	510			[4]				D
18:00	450	540							
Next day					(5)*				

*The PK sample on next day can be taken at any suitable time provided that the exact time of sampling is precisely recorded. **Hyperalgesia testing at the sensitized and contralateral forearm, harmonized across all four IMI2-PainCare-BioPain RCTs. Reproduced from [2]

Procedures, assessments, and events during a period as described previously for RCT3 [2]:
The subject will have breakfast at home and arrive at the site at or before 08:00 AM.Record prior and concomitant medication.Urine screening test for drugs of abuse and alcohol consumption check.For female subjects: urine pregnancy test.Reassess subject eligibility for the study according to inclusion and exclusion criteria.Train / instruct again the subject on the study-specific procedures.Complete PROMs assessing subject expectations.Optionally, according to local practices, an indwelling venous catheter will be inserted at the start of each study period and will be left in place for the duration of the study day.HFS will be applied to the left forearm to induce sensitization.IMP administration.A total of 5 blood samples (6 mL each) will be taken as scheduled in Table 5 for pharmacokinetic (PK) analyses. The last sample will be taken on the next day, at any suitable time.One pre-dose and 3 post-dose PD biomarker assessments will be made as scheduled in Table 5.Hyperalgesia testing at the sensitized and contralateral forearm will be made as scheduled in Table 5, harmonized across all four IMI2-PainCare-BioPain-RCTs.Complete PROMs assessing tiredness and anxiety.Drinks (water or sugared juice, e.g. apple juice) and a light meal will be served as scheduled in Table 5.Instruct the subject not to drive or bike or operate machinery for the entire day (risk of sedation or dizziness caused by IMP). Instruct the participants that they should not drive or bike or operate machinery on the following day if they feel drowsy or dizzy.Upon leaving the trial site, if the subject is feeling drowsy or dizzy, arrange for the participant to be driven home by taxi.

### Follow-up telephone call

Between 7 and 14 days after the end of the last study period, the absence of untoward medical or mental sequelae of the study will be ascertained in a follow-up telephone call with the subject [2].

### Sample size {14}

Knowledge on the variability and effect sizes of excitability parameters is available in amyotrophic lateral sclerosis (ALS) patients with retigabine as treatment [26] as well as in neuropathic pain patients and healthy controls with mexiletine as treatment [27]. Both studies identified group differences between 0.04 and 0.06 ms (0.416 vs. 0.458 on motor nerve excitability [26] and 0.54 vs. 0.60 on sensory nerve measures [27], respectively) and standard deviations around 0.085 (but potentially as high as 0.10) [26, 27]. With the lacosamide vs. placebo comparison of the primary analysis (2-sided type I error of *α*/2 = 0.025) being essentially a paired *t*-test (assumed correlation of 0.5), the following power graphic yields a reasonable sample size, i.e., power > 80% (STATA, StataCorp LCC, USA). The study on large sensory fibers yielded much higher power than the study on motor fibers (Fig. 3, dashed vs. drawn lines), while the range of expected standard deviations had only small effects on power (crosses vs. circles). Based on the worst case, a power of 0.80 would require 48 subjects, while in the best case scenario 22 subjects would be sufficient.

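### The sample size is worked out for single SDTC levels, but the primary endpoint is a change from a period-specific baseline, and its power depends on a same-day correlation the plan never states

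*Protocol article*

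**What the plan says.** Under Primary and key secondary outcomes, the protocol article defines the two primary endpoints, sensory and motor SDTC, "both at the planned first PD time point post dosing relative to their pre-dose PD measurement (i.e., difference to period specific baseline". Table 1 likewise speaks of SDTC changes.

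Under Sample size {14}, the inputs are:
- motor effect: "0.416 vs. 0.458 on motor nerve excitability"
- sensory effect: "0.54 vs. 0.60 on sensory nerve measures"
- spread: "standard deviations around 0.085 (but potentially as high as 0.10"
- test: in essence a paired t-test, with "2-sided type I error of *α*/2 = 0.025" and "assumed correlation of 0.5"

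The result is given as "Based on the worst case, a power of 0.80 would require 48 subjects", with 22 in the best case. Sixty subjects are to be randomized to allow for early dropout. Under Subject discontinuation from the trial, those who leave are not replaced.

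Under Primary analysis of endpoints, the mixed model has treatment, period, center and sequence as fixed effects and compound symmetry across periods. No pre-dose SDTC term is listed.

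**The concern.** The lacosamide-placebo contrast on the primary endpoint is a difference of two differences and uses four measurements per subject. The calculation treats it as a difference of two measurements. Subtracting a pre-dose value removes between-day variation but adds the measurement noise of the baseline. Which effect is larger depends on how closely the same-day pre-dose and post-dose values agree. The sample-size text gives no SD of change and no pre/post correlation, so the claim of more than 80% power is not tied to the endpoint and model described. The motor endpoint is the exposed one, because its assumed effect is the smaller of the two.

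**Working it through.** **Inputs.** Motor effect 0.458 − 0.416 = 0.042 ms. Sensory effect 0.60 − 0.54 = 0.06 ms. SD 0.085 or 0.10. Two-sided alpha 0.025. Lacosamide-placebo correlation 0.5. All are from Sample size {14}. Power is from the exact noncentral t for a paired t-test.

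**1. The plan's own figures.** SD of the paired difference = SD·√(2(1 − 0.5)) = SD.
- Best case (0.06, SD 0.085): n = 22, an exact match. This shows that the quoted SD was entered per measurement, with paired-difference variance SD².
- Worst case (0.042, SD 0.10): n = 57, not 48; power at 48 is 72%. This is a separate discrepancy and should be settled in the same recalculation.

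**2. Variance for the stated endpoint.** Let rw be the same-day pre/post correlation, let every cross-day correlation equal rb, and let SD be that of a level.
- Each change has variance 2·SD²·(1 − rw).
- The covariance of changes in two periods is SD²·(rb − rb − rb + rb) = 0.
- The variance of the difference in changes is therefore 4·SD²·(1 − rw).

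The cross-day correlation cancels, so the plan's 0.5 does not enter. The ratio to the planned SD² is 4(1 − rw), which equals 1 only at rw = 0.75.

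**3. Motor endpoint** (each cell SD 0.085 / 0.10). The documents give no value for rw, so this is a sensitivity range.

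| rw | variance ratio | n for 80% | power, 48 pairs | power, 60 pairs |
|---|---|---|---|---|
| 0.5 | 2.0 | 81 / 111 | 55% / 41% | 66% / 50% |
| 0.6 | 1.6 | 65 / 89 | 65% / 50% | 76% / 61% |
| 0.7 | 1.2 | 50 / 68 | 79% / 63% | 88% / 75% |
| 0.75 | 1.0 | 42 / 57 | 86% / 72% | 93% / 83% |
| 0.8 | 0.8 | 34 / 46 | 93% / 82% | 97% / 91% |

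Solving the same formula for 80% power, rw must be at least about 0.63 / 0.73 with 60 pairs and 0.71 / 0.79 with 48.

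**4. Sensory endpoint.** With 60 pairs, power is 94% (SD 0.085) or about 84% (SD 0.10) at rw 0.5, and higher at larger rw. With 48 pairs it is 87% or 73% at rw 0.5, and 94% or 83% at rw 0.6.

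**5. Effect of a pre-dose covariate.** The post-dose difference and the pre-dose difference each have variance 2·SD²·(1 − rb), and their covariance is 2·SD²·(rw − rb). The within-subject slope is (rw − rb)/(1 − rb). The residual variance is 2·SD²·(1 − rb)·[1 − ((rw − rb)/(1 − rb))²]. At rb = 0.5 this is SD²·[1 − (2rw − 1)²].

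| rw | change score, ×SD² | with covariate, ×SD² |
|---|---|---|
| 0.5 | 2.0 | 1.00 |
| 0.6 | 1.6 | 0.96 |
| 0.7 | 1.2 | 0.84 |
| 0.75 | 1.0 | 0.75 |
| 0.8 | 0.8 | 0.64 |

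Adjustment never exceeds the planned variance and is below the change score at every rw shown. The formula ignores the small cost of estimating the slope.

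**The case against.** A reader might infer that the variance doubles under the plan's own correlation of 0.5 and that the trial is therefore underpowered. The documents do not support this. The plan's 0.5 belongs to the lacosamide-placebo pairing, is never assigned to the same-day pair, and cancels in step 2. Doubling needs rw = 0.5, which is a severe choice. Table 5 places the two PD sessions at −60 and +60 minutes from dosing, two hours apart on one day, whereas periods are at least a week apart. Same-day values may well agree better than values from different weeks, and above rw = 0.75 the plan's calculation is conservative. A high rw is not assured either, since electrodes are placed in each PD session.

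The SD is also not labelled as one of levels. If 0.085 and 0.5 both described changes, the formula would fit the endpoint. The figures printed beside the SD are levels, however, and the text nowhere mentions an SD of change. With equal cross-day correlations, changes in different periods would be uncorrelated, so a correlation of 0.5 would need something more, such as a consistent drift over the day within each subject. This reading is possible but not stated.

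Finally, the two primary tests run in parallel at alpha/2 and either one can succeed alone, so a weak motor test does not sink the trial. The article is also condensed, and a baseline covariate could appear in an analysis plan that is not shown. These points limit the consequence. They do not supply the missing link between the stated power and the stated endpoint.

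**Conclusion.** The point holds in limited form. The power in Sample size {14} is that of a comparison of single levels with paired-difference variance SD². It is not shown for a change from period-specific baseline analysed without a baseline covariate. Taking the SDs as those of levels and the cross-day correlations as equal, the planned variance is met or bettered only if rw is about 0.75 or higher. Over rw 0.5 to 0.8, motor power with all 60 completing ranges from 66% to 97% at SD 0.085 and from 50% to 91% at SD 0.10. Sensory power with 60 pairs stays above 80% throughout, so the risk falls on the motor endpoint. Neither a factor of two nor an underpowered trial is demonstrated, because rw is unknown. The figures use the plan's paired t-test as a stand-in for the mixed model.

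**What to change.** 1. Add the pre-dose SDTC as a covariate in the primary mixed model for both endpoints. Preferably enter it as two terms: the subject's mean baseline, and each period's deviation from that mean, so that the treatment contrast uses the within-subject slope. With cross-day correlation 0.5 this gives variance SD² at rw = 0.5, which is what the calculation assumes, and less above it. Fix this before unblinding.
2. Restate the power on the scale of the endpoint actually analysed. Label the SD as one of levels or of changes, give the same-day correlation (or an SD of change) beside the cross-day one, and show power at 48 and 60 pairs for rw 0.5 to 0.8. Correct or explain the worst-case 48 at the same time.

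The cost is a recalculation and some wording. The pre-dose measurement is already collected and no extra subjects are needed. The stated motor power may become less favourable.

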**Fig. 3 Fig3:**
[figure not shown]
Power as a function of number of pairs (paired *t*-test for mean difference)

To compensate for early dropouts, e.g., during the first period, we plan to randomize a total of 60 subjects (in the sense of being randomized for entering the treatment phase).

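### The worst-case sample size of 48 does not follow from the protocol's own inputs: they require 57 subjects, and 48 give about 72% power rather than 80%

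*Protocol article*

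**What the plan says.** All the inputs are in the Sample size {14} section of the protocol article.

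- **Test and error level:** the lacosamide versus placebo comparison is planned at a "2-sided type I error of *α*/2 = 0.025" and is described as "being essentially a paired *t*-test (assumed correlation of 0.5").
- **Differences:** "0.416 vs. 0.458 on motor nerve excitability" and "0.54 vs. 0.60 on sensory nerve measures".
- **Variability:** "standard deviations around 0.085 (but potentially as high as 0.10").
- **Effect of the SD:** the section says that the "range of expected standard deviations had only small effects on power".
- **Conclusion:** "Based on the worst case, a power of 0.80 would require 48 subjects, while in the best case scenario 22 subjects would be sufficient".

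Under Fig. 3, to allow for early dropouts, the protocol adds that "we plan to randomize a total of 60 subjects". It gives no dropout rate. The section on subject discontinuation says that subjects who leave are not replaced.

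**The concern.** The best and worst cases should be the two ends of the stated inputs: the larger difference with the smaller SD, and the smaller difference with the larger SD. The first gives the stated 22. The second does not give 48.

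The figure matters because motor-fiber SDTC is one of the two primary endpoints, each tested at half of alpha, and the motor comparison is the one that sets the sample size. A reader takes 48 as the number of completers that secures 80% power even under pessimistic assumptions, and takes the step from 48 to 60 as the dropout reserve. If 48 is too low, that reserve is much thinner than it looks. A null motor result from about 48 completers would then be credited with more power than the design provides.

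**Working it through.** **Inputs, all from Sample size {14}**

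- Two-sided alpha per primary test: 0.025.
- Within-subject correlation: 0.5.
- Motor difference: 0.458 − 0.416 = 0.042 ms.
- Sensory difference: 0.60 − 0.54 = 0.06 ms.
- SD: 0.085, up to 0.10.
- Target power: 0.80.

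**Formulas**

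SD of the within-subject difference = SD × √(2(1 − 0.5)) = SD, so the stated SD can be used directly.

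Power of the paired t-test with n pairs = P(|T| > t(0.9875; n − 1)), where T is noncentral t with n − 1 degrees of freedom and noncentrality (difference / SD) × √n.

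**Step 1: reproduce the best case.** Difference 0.06, SD 0.085. At n = 22 the noncentrality is 0.06/0.085 × √22 = 3.311, the critical value is 2.414 and power is 80.7%. At n = 21 power is 78.4%. The smallest n is 22, exactly as stated, which supports this reading of the test, alpha and correlation.

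**Step 2: apply the same method to the worst case.** Difference 0.042, SD 0.10, standardized difference 0.42.

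| n | Noncentrality 0.42 × √n | Power |
|---|---|---|
| 48 | 2.910 | 72.2% |
| 56 | 3.143 | 79.7% |
| 57 | 3.171 | 80.5% |
| 60 | 3.253 | 82.7% |

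The smallest n is 57. The normal approximation, ((2.241 + 0.842)/0.42)² = 53.9, gives 54, so a cruder formula does not explain 48. Using the larger residual degrees of freedom of the four-period model gives 55.

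**Step 3: test the remark about the SD** (two-sided 0.025).

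| Fiber, difference | SD | n for 80% | Power at n = 48 |
|---|---|---|---|
| Motor, 0.042 | 0.085 | 42 | 86.2% |
| Motor, 0.042 | 0.10 | 57 | 72.2% |
| Sensory, 0.06 | 0.085 | 22 | 99.4% |
| Sensory, 0.06 | 0.10 | 29 | 96.4% |

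For motor fibers the SD range moves the requirement by 15 subjects and power at 48 by 14 points. For sensory fibers the effect at 48 is small, but at the stated best-case size of 22 power falls from 80.7% to 65.7%.

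**Step 4: look for a reading that gives 48.**

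| Reading | n | Why it does not rescue the sentence |
|---|---|---|
| 0.042, SD 0.10, two-sided 0.05 | 47 | Contradicts the stated alpha; the best case would become 18, not 22 |
| 0.04, SD 0.085, two-sided 0.025 | 46 | Leaves out the stated upper SD |
| 0.042, SDs 0.085 and 0.10 in the two arms, two-sided 0.025 | 50 | Assumption not stated; power at 48 is 78.5% |
| 0.042, SD 0.091, two-sided 0.025 | 48 | This SD is not in the text |
| 0.04 (rounded), SD 0.10, two-sided 0.025 | 62 | Further away: 67.6% at 48 and 78.5% at 60 |

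**Step 5: dropout reserve within 60.** Taking 48 as the requirement, 60 − 48 = 12 (20%). Taking 57, 60 − 57 = 3 (5%). With the four-period degrees of freedom, 60 − 55 = 5.

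**The case against.** Nobody disputes the arithmetic from the stated inputs. The strongest points on the other side are these.

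- **Fig. 3 is not available here, and the curves behind the worst case are drawn in it.** If the upper curve used an SD near 0.091, 48 would be right, and the SD would indeed matter less. The error might then lie in the description rather than the calculation. This stands as a caveat about where 48 came from. It does not save the sentence, because the range named in the text runs to 0.10.
- **The protocol never states a 20% dropout allowance.** Correct: 12 of 60 is inferred from the two figures. The primary mixed model also uses all available periods, so a late dropout need not cost a lacosamide–placebo pair. The reserve of 3 is therefore an approximation based on complete pairs.
- **The SD remark covers both fiber types and is fair for sensory fibers at 48.** That is so, but it fails for the motor endpoint, which sets the sample size.
- **The plan randomizes 60, which gives 82.7% in the worst case and 93% at SD 0.085, so the target above 80% is met.** This holds if nearly all subjects complete, and it is why no larger trial is asked for. It is also true that a null result should be read from its confidence interval, which the protocol promises. Neither point makes 48 correct.

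**Conclusion.** The concern holds: the worst-case figure is wrong as written. With a difference of 0.042 ms, SD 0.10, correlation 0.5 and two-sided 0.025, 80% power needs 57 subjects. The stated 48 is 9 too few and gives 72.2%. With 60 completers power is 82.7%, so the planned number randomized remains defensible, but with a worst-case reserve of about 3 subjects.

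The conclusion rests only on the inputs printed in the section and on a paired t-test, which the protocol itself takes as the approximation to its primary analysis. The exact match of the best case supports that reading. The source of 48 cannot be settled without Fig. 3. An SD near 0.091 would produce it; an unsplit alpha of 0.05 comes close at 47 but is hard to square with the stated 22. The sensory primary comparison is not affected: at 48 subjects its power is 96% even with SD 0.10.

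**What to change.** Correct the paragraph in Sample size {14}:

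1. State that the worst case (0.042 ms, SD 0.10, correlation 0.5, two-sided 0.025) requires 57 subjects, and that power is 72% with 48 completers and 83% with 60.
2. Delete the statement that the SD range has little effect on power, or limit it to sensory fibers at the planned size and report the motor figures (42 versus 57 subjects).
3. State that the worst-case dropout reserve within 60 is about 3 subjects on a complete-pair basis.
4. If 48 was read from a curve with a different SD, name that SD and do not call it the worst case while 0.10 remains in the text.

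The cost is one corrected paragraph and a less favorable stated figure. Enrolment, conduct and analysis do not change.
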